## 8.3 Follow-up Visits

### 8.3.1 Initial Follow-up

Follow-up will occur ~15 minutes; and ~30min (for stage C1b only) after antigen administration. Each skin test site will be examined by the administrator or other qualified staff member, for leakage, bleeding, or other local reactions (pain, erythematous, urticaria, and angioedema). In addition, subjects are asked if they are feeling faint, nauseated, or short of breath. Indication of symptoms will be recorded on the 15 Minute and 30 minute Reaction Record Form as “yes” or “no”. If any of the symptoms are classified as an adverse event (see Section 11.2.1.2, “Management of Possible Adverse Events”), the Adverse Events Form must be completed. If the symptom is a Serious Adverse Event (see Section 11.2.1.3, “Management of Possible Serious Adverse Events”), the SAE Form must be completed as well. After the initial follow-up examination, it will be determined whether the subject is fit to be discharged. A “yes” or “no” will be marked on the 30 – Minute Reaction Record Form to indicate suitability for discharge. If the subject is not ready to be discharged, the AE Form and SAE Form (depending on severity of the event) must be completed. If the subject is ready to be discharged s/he will be given exact instructions regarding where and when to return for the next skin test reading, and will be given a contact phone number in case of emergency or if the subject cannot come to the test reading session.

Refer to Appendix A, Schedule of Procedures/Evaluations, for a detailed list of the sequence of events and evaluations that should occur during enrollment, administration of study product, and the follow-up.

### **8.3.2 Subsequent Follow-up**

Subsequent follow-up visits to measure reactogenicity of skin test antigens and to monitor subject health will follow at 45-51h (Stage A only), 2-4 days, and 6-8 days (Stages B and C, only). Any subject with an induration of greater than 10 mm in diameter, observed during any of these readings, will be asked to return at 25-31 days for follow-up. Those subjects who need to return at day 25-31 will have their study/subject number posted on the bulletin board of the appropriate college/campus (primarily healthy non-contacts in all stages) and/or will be given instructions and a card indicating the date of their next visit (primarily patients and contacts of leprosy patients in Stage C) to serve as a reminder, without revealing the identity of the subject. Subjects experiencing any persistent reaction or adverse event will be followed until the resolution or stabilization of symptoms.

The method for measuring reactogenicity has been previously described in Section 4.5, "Methods for Collecting Data for Assessment of Study Objectives". At each reading session, subjects will be interviewed and examined by an MO, nurse, or paramedic. Reactogenicity will be assessed, and measurements of induration (mm) and extent of erythema (Stage B, C-1 and C-1b, only) will be recorded for each subject on the Skin Test Reading Form. A Follow-up Examination and Reaction Form will then be completed, similar to the 15 Minute Follow-up Form. The presence of symptoms including pain, erythema, bleeding, urticaria, infection, and blistering/ulcerations at each test site will be recorded as "yes" or "no". A physical examination of the axillary lymph node will be performed and results (normal, painful, swollen, lymphangitis, or tender) will be indicated. If any of the symptoms are suspicious of an AE and/or SAE, the attending physician will examine the subject and complete the AE Form and/or SAE Form, if applicable. The subject's axillary temperature will be taken using a thermometer placed under the arm pit and recorded. If the subject has a fever ( $\geq 104^{\circ}\text{F}$ ) for more than 3 hours, both an AE and SAE Form must be completed. Upon completion of the follow-up examination, a "yes" or "no" will be marked on the Follow-Up Examination and Reaction Form to indicate subject suitability for discharge. Indications for discharge have been previously described (see Section 8.3.1, "Initial Follow-Up").

In addition to interviewing and examining subjects for reactogenicity and adverse events, each subject in Stages A and B only will be asked to complete a Symptom Diary Card. Records of local and systemic reactions, including pain, swelling, redness, itching, blistering, or swollen lymph nodes, that occur on the day of the skin test and subsequent days following the skin test (three days for Stage A and seven days for Stage B), will be recorded. The subject will submit the Diary Card to the SC at the day 7 reading for review by the SC and/or the MO. Data from the Symptom Diary will not be entered into the study database, unless relevant information such as an AE is recorded. Any findings of relevance will be entered into the appropriate CRF (Follow-up Form, and/or AE Form).

The specific sequence of follow-up events includes:

- Day 0 (Stages A, B and C)
  - Screening
  - Enrolling
  - Blood sampling - Stage C only
  - Randomization
  - Study Product Administration Form
  - Complete the 15 minute follow-up
    - Interview
    - Examine skin test sites
  - Complete the 30 minute follow up (stage C1b only)
    - Interview
    - Examine skin test sites
    - Determine subject suitability to discharge
      - If not ready to discharge
        - Complete AE
        - Complete SAE, if needed
      - If subject is ready to discharge
        - Remind subject of next reading
        - Provide subjects (Stages A and B) with Symptom Diary Cards
- Day 2 is 48h ± 3h post antigen administration (Stage A, only)
  - Complete Skin Test Reading Form
    - Measure induration
  - Complete the Follow-Up Examination and Reaction Record
  - Interview subject
    - Examine skin test sites
    - Determine subject suitability to discharge
      - If not ready to discharge
        - Complete AE
        - Complete SAE, if needed
      - If subject is ready to discharge
        - Remind subject of next reading
- Day 3 ± 3h post antigen administration (Stage A and B) or ± 1 day post antigen administration (Stage C)
  - Review Symptom Diary Cards and collect - Stage A, only
  - Complete Skin Test Reading Form
    - Measure induration
    - Measure erythema (Stage B and C, only)
  - Complete the Follow-Up Examination and Reaction Record

- Interview subject
  - Examine skin test sites
  - Determine subject suitability to discharge
    - ❑ If not ready to discharge
      - Complete AE
      - Complete SAE, if needed
    - ❑ If subject is ready to discharge
      - Remind subject of next reading
- 
- Day 7  $\pm$  1 day post antigen administration (Stages B and C)
  - Review Symptom Diary Cards and collect – Stage B, only
  - Complete Skin Test Reading Form
    - Measure induration
    - Measure erythema
  - Complete the Follow-Up Examination and Reaction Record
    - Interview subject
    - Examine skin test sites
    - Determine subject suitability to discharge
      - ❑ If not ready to discharge,
        - Complete AE
        - Complete SAE, if needed
      - ❑ If subject is ready to discharge
        - Remind subject of next reading, if applicable
        - Study Termination, if applicable
- 
- Day 28  $\pm$  3 days post antigen administration (Stage A, B and C – Subjects with an induration greater than 10mm at any reading)
  - Complete Skin Test Reading Form
    - Measure induration
    - Measure erythema
  - Complete the Follow-Up Examination and Reaction Record
    - Interview subject
    - Examine skin test sites
    - Determine subject suitability to discharge
      - ❑ If not ready to discharge
        - Complete AE
        - Complete SAE, if needed
      - ❑ If subject is ready to discharge
        - Study Termination

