### **3.4 Method of Assessing Study Outcome**

The injection sites for all skin test antigens in the 260 individuals in this Phase II study (10 from Stage A, 90 from Stage B, and 160 from Stage C) will be evaluated by the same methods used to determine the response to tuberculin/PPD, i.e., evaluation of induration and erythema. The results from the healthy non-contacts studied in Stages A and B will be grouped. The results from this entire group will be compared to the results from the clinical leprosy patients, contacts of leprosy patients, and clinical tuberculosis patients in Stage C-1 and C-1b. Blood samples from each subject in Stage C will be collected to perform leprosy specific serology and blood based gamma interferon test.

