## 4.5 Methods for Collecting Data for Assessment of Study Objectives

Administration of antigens and reading of induration will normally be performed by separate teams, although it will be acceptable for an administrator to also be a reader of the same subject. Administrators and readers will be blinded to the antigen identity at each site. Each antigen site will be read and recorded by two independent readers at ~15 min, 45-51 h and 69-75 h for Stage A, and ~15 min, 69-75 h, and 6-8 days for Stage B, ~15 min, ~30 min (for stage C1b only), 2-4 days, and 6-8 days for Stage C. The method for reading will be as follows: The site will be gently palpated, the limits of the induration determined with the fingers, and the largest transverse diameter will be measured with a soft, flexible, transparent ruler by two independent readers. The maximal diameter will be recorded by each reader, and an average of the two will be used. Readings from both readers will be analyzed for correlation (the most experienced administrator/reader will be used as the 'gold standard'). In the case that there are systematic reading errors on the part of the second reader, the reader will be given more supervision. In the case that the second reader shows 'terminal digit preference' in his/her readings (i.e., his/her readings always end in an even or odd number), further training will be given without explaining to the reader the reason for the additional training, in order to avoid correcting one bias by potentially introducing another [adapted from "Guidelines for Conducting Skin Test Surveys in High Prevalence Countries," issued by the International Union Against Tuberculosis and Lung Disease (24)]. Erythema will also be measured (by ruler) and recorded at each time point.

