### 13.4 Study Outcome Measures

The primary outcome measure of this study is induration resulting from the skin test antigen DTH response. The method for measuring induration has been described in Section 4.5, "Methods for Collecting Data for Assessment of Study Objectives". As mentioned previously, evaluation of this observation variable will be performed using the same techniques used to evaluate the tuberculin/PPD response. A tuberculin reaction greater than 10mm of induration is classified as positive for persons who are not immunocompromised or previously in contact with TB patients, but have other risk factors for TB, such as living in a country where TB is prevalent. Induration measurements will be taken on days 2 and 3 (Stage A) and days 3 and 7 (Stage B and C) after skin test administration, at each test antigen site. If a subject is observed to have an induration greater than 10 mm at any injection site, at either study visit, they will

be asked to return at 25-31 days for a final induration measurement. Any reaction that persists will be followed-up until resolved or stabilized.

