|---------------|-----------------------------------------------------------------------|----------------------------------------------------------------------------------------------------------------------|
| Day -10 to -1 | Informational seminar and recruitment of volunteers                   | Informational seminar and recruitment of volunteers                                                                  |
| Day 0         | Pregnancy test for women                                              | Pregnancy test for women                                                                                             |
| Day 0         | Skin test antigens will be administered; first reading at ~15 minutes | Skin test antigens will be administered; readings at ~15 minutes and ~30 min (30 minute reading for stage C1b only). |
| Day 2         | 48 h reading, Part A only                                             | none                                                                                                                 |
| Day 3         | 72 h reading                                                          | 72 h reading                                                                                                         |
| Day 7         | 7 d reading                                                           | 7 d reading                                                                                                          |
|               |                                                                       |                                                                                                                      |
| Day 25 to 31  | 28 d reading for positive reactors                                    | 28 d reading for positive reactors                                                                                   |

---

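### The early induration reading has a 6-hour window in healthy subjects and a two-day window in every Stage C group, so reading time can differ by group in the healthy-versus-Stage C comparison

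*Protocol*

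**What the plan says.** **Windows.** Protocol Section 4.5 reads Stage A at "45-51 h and 69-75 h for Stage A", Stage B at 69-75 h and 6-8 days, and Stage C at "2-4 days, and 6-8 days for Stage C". The visit list in Section 8.3.2 gives the early reading as "Day 3 ± 3h post antigen administration (Stage A and B) or ± 1 day post antigen administration (Stage C"). Sections 5.1.6 and 10.1 and Appendix A agree with this.

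**Statements that do not match.** The opening paragraph of Section 8.3.2 gives "45-51h (Stage A only), 2-4 days, and 6-8 days (Stages B and C, only"), with no 69-75 h limit for Stages A and B. Section 13.4 names nominal days only: "Induration measurements will be taken on days 2 and 3 (Stage A) and days 3 and 7 (Stage B and C"). The Section 4.4 table also shows day 3 with no window. Appendix C calls the Stage C reading a 72 h reading. Its day 2 row has "48 h reading, Part A only" for Stages A and B and no reading for Stage C.

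**Use of the readings.** Section 3.4 pools the healthy non-contacts of Stages A and B and says: "The results from this entire group will be compared to the results from the clinical leprosy patients", as well as with contacts and TB patients. Section 3.1 makes the comparison of positive proportions part of a primary objective. Section 4.1 uses non-contact reactions as the baseline that helps set the cut-off. Section 10.1 says comparisons with healthy volunteers will inform sensitivity and specificity. Section 4.6 lists covariates group by group, and hours from injection to reading is not among them.

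**The concern.** Healthy status and reading window coincide completely. No healthy non-contact is in Stage C, and no patient or contact is in Stages A or B. Campus volunteers must be read within three hours of 72 h, whereas a leprosy, TB or contact subject may be read on day 2, 3 or 4. The protocol treats 48 h and 72 h as two separate readings in Stage A, yet a Stage C reading at either time fills the same slot.

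If Stage C readings tended to fall early or late, and if induration changes over those days, part of any healthy-versus-Stage C difference would be a timing effect. It would enter the comparison of positive proportions and any cut-off built partly on the Stage A and B data. The listed covariates would not remove it.

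**Working it through.** **1. Windows (Sections 4.5 and 8.3.2, Appendix A).**
- Stages A and B: 72 ± 3 h = 69 to 75 h, width 6 h.
- Stage C: day 3 ± 1 day, taken as 72 ± 24 h = 48 to 96 h, width 48 h.
- Ratio 48/6 = 8, with the same centre of 72 h.
- If Stage C times were spread evenly, the share outside 69-75 h would be 1 − 6/48 = 87.5%.

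**2. Who is affected (Sections 3.4 and 4.2).** Healthy: 10 + 90 = 100, all on the narrow window. Stage C: 80 + 80 = 160, all on the wide one.

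**3. Which reading is shared.** Stage A has 48 h and 72 h, Stage B has 72 h and day 7, and Stage C has day 2-4 and day 6-8. The day 3 reading is the only one after day 0 that all three stages are scheduled to have. The day 6-8 window is identical in Stages B and C.

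**4. Size of a possible bias (assumptions, not protocol figures).** Let induration at 72 h be normal with mean m and SD s, drifting linearly by b mm per day. For a reading d days from 72 h:

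P(>10 mm) = Φ((m + b·d − 10)/s)

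The grid was m = 8, 10, 12 mm; s = 4, 6 mm; b = 1, 2, 3 mm/day.

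| Reading times | Result |
|---|---|
| 69-75 h | within 0.001 of the 72 h value throughout |
| 48-96 h, evenly spread | at most about 1.5 points (m = 8, s = 4, b = 3: 0.309 to 0.324; m = 12, s = 4, b = 3: 0.691 to 0.676) |
| All at one end | about 6 points (m = 8, s = 6, b = 1: 0.369 to 0.309 at day 2) to 29 points (m = 8, s = 4, b = 3: 0.309 to 0.599 at day 4) |

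A middle case is m = 10, s = 4, b = 2. It gives Φ(0) = 0.50 at 72 h, Φ(−0.5) = 0.31 at day 2 and Φ(0.5) = 0.69 at day 4. With an even spread it stays at 0.50.

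A symmetric but extreme split, half at day 2 and half at day 4, gives (0.106 + 0.599)/2 = 0.353 against 0.309 for m = 8, s = 4, b = 3, or about 4 points. A wide window alone therefore does modest harm in this model. A systematic shift in when Stage C subjects are read does more.

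**The case against.** The strongest reply is that the windows differ in spread, not in target. Both aim at 72 h, and the documents contain neither actual reading times nor a time course of induration for these antigens. That stands: bias is possible but not shown.

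Several further replies also stand in part.

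- **Deciding reading.** A reader might infer that the early reading is the one that makes a test positive. The protocol does not say so. Sections 4.5 and 8.4 count a reaction above 10 mm at any reading for follow-up, Section 13.6 names no time point for the primary variable, and the cut-off is still to be derived (Section 13.9.3).
- **Scope.** A reader might infer that all the sensitivity, specificity and ROC work is confounded with reading time. The contrasts sized in Section 13.6.2 lie within C-1 or C-1b, where all groups share one window. The mismatch reaches only results that use the Stage A and B healthy subjects. That is still a real set, given Sections 3.1, 4.1 and 10.1.
- **Matched reading.** For 90 of the 100 healthy subjects (Stage B), the day 6-8 reading has the same window as in Stage C.
- **Labels.** Section 13.4, the Section 4.4 table and Appendix C can be read as visit names rather than windows. That is fair. The opening paragraph of Section 8.3.2 is different, because it states a window and omits the limit for Stages A and B.
- **Descriptive study.** Section 13.5 disclaims formal testing, and the choice of analysis time point may sit in an analysis plan that was not available. The windows and the covariate list, however, are fixed in the protocol itself.

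**Conclusion.** The concern holds in a limited form. The protocol permits the early reading to differ systematically in time between healthy non-contacts and every Stage C group, it uses that comparison for a primary objective and to help set the cut-off, and its covariate list does not include elapsed time.

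The size is unknown from the documents. Under the stated assumptions it runs from at most about 1.5 points in the proportion above 10 mm, if Stage C times are spread evenly, to about 6 to 29 points if they all fall at one end. The upper figures need both a one-sided shift and a drift of 1 to 3 mm per day; neither is documented. The data can help judge this: Stage A gives paired 48 h and 72 h readings, though in only 10 healthy subjects.

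This is worth correcting because the remedy is cheap. It does not invalidate the design, and it does not touch the contrasts made wholly within Stage C.

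**What to change.** 1. **Remaining C-1b subjects.** Aim the early reading at 69-75 h and keep day 2-4 as the fallback. Section 13.7 says Stages A, B and C-1 are complete, so scheduling can change for at most the 80 C-1b subjects.
2. **Analysis.** Keep all C-1 and C-1b readings in the main analysis. In any comparison or cut-off that uses Stage A and B healthy subjects, either adjust for actual hours from injection to reading, or report results with and without Stage C readings outside 69-75 h.
3. **Common reading.** Use the day 3 reading for all groups in that comparison, because Stage A has no day 7 reading. Give the matched day 6-8 reading of Stages B and C as a supporting analysis.
4. **Text.** Reconcile the opening paragraph of Section 8.3.2 with the visit list in the same section, and align the Section 4.4 table, Section 13.4 and Appendix C with the stated windows.

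Making 69-75 h the only classifying window is not advised, because it could discard much of the completed C-1 data. With evenly spread times, about 20 × 0.125 = 2.5 of 20 subjects per group would remain.

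The cost is one extra analysis, slightly tighter C-1b booking and wording changes. The restricted analysis may be imprecise if few C-1 readings fall inside 69-75 h. The protocol does not say whether the clock time of each C-1 reading was recorded; if only the date was, the adjustment has to use days.

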## 8.4 Final Study Visit

The final study visit will be at 69-75h (Stage A) or day 6-8 (Stage B and C), unless a positive reaction of greater than 10 mm in diameter is measured during this or any prior visit, or if an SAE or AE is on-going. In this event, the subject will be asked to return for a final visit on day 25-31 for examination and/or measurement of the skin test sites. Any reaction or event that persists will be followed-up until resolved or stabilized. Following the final subject interview and examination of skin test sites, the Termination Study Form will be completed, and the subject will be released from the study. At this time, in return for their time and inconvenience, subjects will receive a small gift valued at approximately US\$11.

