## 4.4 Sequence and Expected Duration of Subject Participation

Subject participation for each stage of the trial will be 7 days ( $\pm 1$  day). If induration  $> 10$ mm at any injection site is observed during the first 7 days, involvement in the study will last for 28 days ( $\pm 3$  days) or until all reactions are resolved or stabilized. Total time involvement for each participant is approximately 5.0 hours, as follows:

| Trial Period  | Description                                              | Stage |   |     |     |  | Est.
Duration
(hours) |
|---------------|----------------------------------------------------------|-------|---|-----|-----|--|-----------------------------|
|               |                                                          | A     | B | C1a | C1b |  |                             |
| Day –10 to –1 | Description of the study to allow informed consent       | X     | X | X   | X   |  | 1.00                        |
| Day 0         | Informed consent process                                 | X     | X | X   | X   |  | 0.50                        |
|               | Screening:                                               | X     | X | X   | X   |  | 1.50                        |
|               | Health Questionnaire/History Form                        |       |   |     |     |  |                             |
|               | Physical Examination                                     |       |   |     |     |  |                             |
|               | Eligibility Checklist/Enrollment                         | X     | X | X   | X   |  | 0.25                        |
|               | Blood Sampling                                           |       |   | X   | X   |  | 0.25                        |
| Day 0         | Administration of antigen                                | X     | X | X   | X   |  | 0.25                        |
|               | Reaction recorded ~15min and 30 min (for stage C1b only) |       |   |     |     |  | 0.25                        |
| Day 2         | Reading skin tests                                       | X     |   |     |     |  | 0.25                        |
| Day 3         | Reading skin tests                                       | X     | X | X   | X   |  | 0.25                        |
| Day 7         | Reading skin tests                                       |       | X | X   | X   |  | 0.25                        |

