##### 11.2.1.1 Definitions

###### 11.2.1.1.1 Adverse Event (AE)

An AE is any untoward medical occurrence in a patient or clinical investigation subject to whom a pharmaceutical product has been administered, and that does not necessarily have a causal relationship with this treatment. An AE can therefore be

any unfavorable and unintended sign (including an abnormal laboratory finding), symptom, or disease temporally associated with the use of a medicinal (investigational) product, whether or not in association to the medicinal (investigational) product, within a specified period of time. The occurrence of an adverse event may come to the attention of study personnel during study visits and interviews or by a study recipient presenting for medical care.

All adverse events must be graded for intensity and relationship to study product.

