#### **11.2.1.1.2 Serious Adverse Event (SAE)**

An SAE is any untoward medical occurrence within a specified period of time that at any dose:

- Results in death.
- Is life-threatening. Any adverse therapy experience that places the subject, in the view of the investigator, at immediate risk of death from the reaction as it occurred (i.e., it does not include a reaction that, had it occurred in a more serious form, might have caused death).
- Requires in-patient hospitalization or prolongation of existing hospitalization.
- Results in persistent or significant disability or incapacity.
- Is a congenital anomaly/birth defect.
- An event that required intervention to prevent permanent impairment or damage.

Important medical events that do not result in death, are not life-threatening, or do not require hospitalization may be considered serious adverse events when, based upon appropriate medical judgment, they might jeopardize the subject and might require medical or surgical intervention to prevent one of the outcomes listed above.

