## **11.3 Reporting Procedures**

### **11.3.1 Adverse Events**

Adverse Events including local and systemic reactions not meeting the criteria for “serious adverse events” should be captured on the appropriate case report form. Information to be collected includes event description, time of onset, investigator assessment of severity, relationship to study product, time of resolution of the event, seriousness, and outcome. All adverse events occurring while on study must be documented appropriately regardless of relationship. All AEs will be followed to stabilization, if they do not resolve. An event is reportable as associated with the product if the possibility of a relationship of the product to the event cannot be ruled out.

Any medical condition that is present at the time that the subject is screened should be considered as baseline and not reported as an AE. However, if it deteriorates at any time during the study it should be recorded as an AE.

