Ethical concerns have been taken into account for each group of volunteers. It is expected that healthy non-contacts, tuberculosis patients, and some BL/LL patients may have small (less than 10mm) induration reactions to the leprosy skin test antigens, due to cross-reactivity with *M. tuberculosis*, BCG vaccination, and/or environmental mycobacteria. Known environmental mycobacteria present in soil and water include: *M. avium-intracellulare*, *M. kansasii*, *M. xenopi*, *M. ulcerans*, *M. marinum*, *M. malmoense*, *M. fortuitum*, and *M. chelonae*. Tuberculosis patients are expected to produce a strong induration (10-30mm) response to PPD, however, the reaction is not expected to develop into an AE based on previous PPD testing in this region. Since tuberculosis is prevalent in Nepal and many individuals were vaccinated with BCG, most subjects will have been exposed to tuberculosis antigens, and therefore the remaining groups (healthy non-contacts, BL/LL and BT/TT leprosy patients, and contacts of leprosy patients) may react to PPD. Hence, PPD testing will be a measure of not only exposure to tuberculosis, but also BCG vaccination, and/or non-pathogenic environmental mycobacteria, to some extent. Finally, BT/TT leprosy patients and healthy contacts of leprosy patients are expected to respond more strongly (greater than 10mm induration) to leprosy skin test antigens. In order to minimize the risk to these groups, a preliminary test of each antigen at the high dose (1.0µg/100µl) will be tested in a small group of 20 subjects from each group, except the healthy non-contacts (Stage C-1). If serious adverse events are indicated, the causative antigen or antigen dose will be dropped from the study, following a safety review. To provide a comparative population at the low dose (0.1µg/100µl), Stage C-1b will be performed. Overall, the anticipated risks are the same as those encountered with other intradermal antigens such as tuberculin (see Section 2.3.1.1, "Skin Testing Risks").

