### **13.8.3 Safety Outcomes**

The following safety outcome measures will be monitored: Measurement of induration, indication of erythema, measurement of local reactions, measurement of systematic reactions, and monitoring for AEs and SAEs. Each measure of safety is controlled by specifications for an AE and SAE. Monitoring safety outcome measures is performed during each study visit, up to day 3 for Stage A, and up to day 7 for Stages B and C. Reactions to the antigens that are assessed as being severe will be followed-up to day 28, or until resolved or stabilized. If a subject responds to any skin test antigen greater than 10mm in

diameter at any study visit, they will be followed-up to day 28, or until resolved or stabilized.

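### All-AE counts and day 25-31 reaction data cover windows that depend on induration; comparisons between groups, and of C-1 with C-1b, need a common cut-off at the day 6-8 visit

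*Protocol*

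**What the plan says.** **Length of follow-up.** Under section 8.4 the last visit is at 69-75 h in Stage A and day 6-8 in Stages B and C, "unless a positive reaction of greater than 10 mm in diameter is measured during this or any prior visit". An ongoing AE or SAE is a second trigger. Section 4.4 makes clear that every site counts, PPD included: if induration above 10 mm "at any injection site is observed during the first 7 days, involvement in the study will last for 28 days" (±3 days). Section 8.3.2 gives the content of the day 28 visit: reading, interview, examination, and AE and SAE forms if needed.

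**Outcome.** The trigger variable is also the main endpoint (section 13.4): "The primary outcome measure of this study is induration resulting from the skin test antigen DTH response".

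**AE period.** The AE definition in section 11.2.1.1.1 covers events whether or not they are "in association to the medicinal (investigational) product, within a specified period of time". The SAE definition reads "An SAE is any untoward medical occurrence within a specified period of time that at any dose". Section 11 does not say how long that period is. Section 11.3.1 states the collection rule: "All adverse events occurring while on study must be documented appropriately regardless of relationship". Section 13.8.3 says that safety monitoring "is performed during each study visit, up to day 3 for Stage A, and up to day 7 for Stages B and C", and then extends it to day 28 or resolution for severe reactions and for any reaction above 10 mm.

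**Analysis.** Section 13.9.2 summarises local reactions by time point and antigen, compares them across groups if rates are high, and considers a GEE logistic model. It tabulates AEs by relationship, intensity and MedDRA term, with no cut-off day. Section 13.6.1 allows C-1 and C-1b to be combined if the event probabilities are similar.

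**The concern.** After the day 6-8 visit, events are sought at a scheduled visit only in subjects who are asked back, and the usual reason for asking them back is the size of the skin reaction. A group or stage with fewer reactions above 10 mm is therefore watched for less time and can show fewer AEs at the same underlying rate.

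The protocol gives reasons to expect the recalled share to differ. Section 13.2 says "Tuberculosis patients are expected to produce a strong induration (10-30mm) response to PPD". It expects more than 10 mm to the leprosy antigens in BT/TT patients and contacts, and smaller reactions to those antigens in non-contacts and some BL/LL patients. C-1b uses a tenfold lower antigen dose than C-1, and the PPD dose was reduced from 5 TU to 2 TU during C-1. If fewer C-1b subjects exceed 10 mm, the low dose is observed for less time, which could make it look safer than it is.

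Safety is a primary objective, and the SMC reviews it stage by stage. The same problem affects reaction proportions at day 25-31, which describe only those asked back. It also affects a GEE model that includes that visit, because whether the record exists depends on earlier induration.

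**Working it through.** **1. The protocol's own safety figure.** Section 13.6.1 gives the chance of at least one event as 1 − (1 − p)^n. With p = 0.10 and n = 18 this is 1 − 0.9^18 = 84.99%, as printed. With n = 36 it is 97.75%, also as printed. Both reproduce, but p has no time period attached, so these tables do not settle which window is meant.

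**2. Window lengths.**
- Stages B and C, nominal: 28/7 = 4.0. At the visit limits: 25/8 = 3.1 to 31/6 = 5.2.
- Stage A, nominal: 28/3 = about 9.

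**3. Observation time in C-1 and C-1b.** Let r be the share followed to day 28. The protocol does not give r, so the values below are assumptions. Ignoring losses, subject-days in 80 subjects = 80 × (28r + 7(1 − r)).

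| r in C-1 | r in C-1b | Subject-days C-1 | Subject-days C-1b | Less observation in C-1b |
|---|---|---|---|---|
| 60% | 40% | 1568 | 1232 | 21% |
| 80% | 30% | 1904 | 1064 | 44% |

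**4. Apparent AE risk when the true rates are equal.** Assume a constant daily rate with a 7-day risk of 5%. The 28-day risk is then 1 − 0.95^4 = 18.55%. The observed risk in a group with share f above 10 mm is (1 − f) × 5% + f × 18.55%.
- f = 20% against 50%: 7.7% against 11.8%, ratio 1.5.
- f = 10% against 80%: 6.4% against 15.8%, ratio 2.5.

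If no AE starts after day 7, every one of these ratios is 1.0.

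**5. With a common 7-day cut.** Both groups show 5%, ratio 1.0, whatever f is.

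**6. Contrasts that are not affected.**
- Reaction proportions at day 3 and day 7: the visits are scheduled for every Stage B and C subject and summarised by time point.
- The two doses of one antigen in Stages A and B, and the two antigens in Stage C: both are given to the same subject, so they share that subject's window.
- Induration itself: it is read at fixed early visits in everyone.

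What remains exposed is all-AE counts and day 25-31 data, when compared between study groups or between C-1 and C-1b, or when pooled.

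**The case against.** **The protocol is not silent on the period.** Section 13.8.3 gives day 3 and day 7, and section 10.1 lists the assessment days. This stands: a reader might infer that no window exists, and that would be wrong. But section 13.8.3 does not call this the AE/SAE period, and it extends it for the same reactions above 10 mm.

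**Section 13.9.2 does not promise all-AE rates by group or dose.** Correct. The group comparison it names concerns local reactions, and section 13.9 plans within-group and combined analyses only where appropriate. The point therefore covers comparisons and pooling that the protocol permits, not a committed AE test.

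**The size rests on assumptions.** This also stands. One could go further and say that the 85% detection chance falls to 37.8%, because 1 − 0.9^(18 × 0.25) = 37.8% if nobody is followed past day 7. The documents do not support that: it reads the 10% as a 28-day risk, which section 13.6.1 never says, and assumes a constant rate. It also sets the recalled share to zero, although PPD is given in both stages and TB patients are expected to react to it. Section 2.3.1.1 places ulceration and necrosis in strong reactors, whom the rule follows longer. Nothing in the protocol shows whether these antigens cause late lesions in weak reactors.

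**Later events are not necessarily lost.** Subjects have an emergency number, and the AE definition includes events found when a subject seeks care. Late events can still be reported, though they are not sought.

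**A tabulation cut-off belongs in the SAP.** It could be placed there, and the SAP is not shown. The period in the AE and SAE definitions is a protocol matter, and the collection rule is what creates the unequal windows.

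**Conclusion.** The point holds in a limited form. Collection while on study, combined with a follow-up length that depends on induration at any site or on an ongoing AE, gives unequal windows for all-AE counts and day 25-31 reaction data. This matters when study groups, or C-1 and C-1b, are compared or combined.

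Only the 4-fold nominal difference in follow-up between subjects in Stages B and C comes from the document. The apparent risk ratios of 1.5 and 2.5 show what is possible under a constant rate, a 5% 7-day risk and assumed recall shares; they are not estimates. The effect is small if nearly all AEs start within 7 days, or if PPD brings similar shares back in every group. The direction against C-1 is plausible but not certain.

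A reader might infer that the low dose will falsely appear safer, or that the safety sample size fails. Neither follows from the text. The correction is still worth making, because it removes the dependence on the recalled share at almost no cost.

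**What to change.** **Section 13.9.2.** Limit comparisons between groups, comparisons of C-1 with C-1b, pooling, and any GEE model of AEs and reactions to onset up to the day 6-8 visit. Use 69-75 h when Stage A is included. List later events separately, with the number of subjects examined at day 25-31 in each group. Draw no comparative conclusion from day 25-31 data.

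**Section 11.2.1.1.** State the same common period in place of the unspecified one, consistent with section 13.8.3. Follow-up of severe or large reactions to resolution stays as it is.

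**Cost.** No new data, visits or consent changes. Section 13.9.2 already lists AE onset date and time, so the cut can also be applied to the completed Stages A, B and C-1. The text edits go through the usual amendment review under section 16.2.

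**Optional, not required.** A day 28 contact for every C-1b subject would equalise follow-up within that stage. It could not be matched in completed C-1, and it would need consent changes and approval by both review boards.
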